### Statistical analysis

No interim analysis is planned.

Baseline characteristics of patients will be described according to group of intervention. Continuous variables will be summarized using descriptive statistics, i.e. number of subjects, mean, median, standard deviation (SD), interquartile range, minimum and maximum. Qualitative variables will be summarized by frequency and percentage. Since this is a non-inferiority study, analysis of the principal criterion will be performed on a per-protocol population. Secondary analysis will be performed based on the intention-to-treat (ITT) principle. VTE events will be defined by: DVT (assessed by proximal compression ultrasonography) or PE (a CTPA or angiography showing intraluminal defect, or a V/Q lung scan showing a high-probability pattern). The decision rule will be based on the upper bound of the 90 % 2-sided CI of the difference of percentage of VTE events between groups. If the upper bound of the CI is above the 1.5 % of difference, the non-inferiority hypothesis of the intervention group will be rejected. The Dunnett and Gent chi square test will also be performed. Secondary analysis will be performed on the ITT population. Considering cluster randomization, confirmatory analysis will be performed using a generalized estimating equation (GEE) assuming an exchangeable correlation matrix structure and considering clustering at the site level. Secondary criteria will be compared under superiority hypothesis and on the ITT population. Descriptive analysis will be performed. Superiority approach will be used to compare secondary evaluation criteria between groups. The ED length stay and the mean proportion of hospital admissions following the ED visit will be compared using a mixed model, considering “center” as random effect. Unnecessary irradiative imaging, adverse events and deaths at 3 months will be compared using GEE assuming an exchangeable correlation matrix structure and considering clustering at site level. All superiority tests will be performed at 5 %. Pre-specified secondary analysis will include comparison of gestalt, Wells’ score and RGS, and performances of the PERC35 score for patients aged under 35 years [38]. Missing data will not be replaced except for the principal criteria for the secondary ITT analysis. Missing value will be considered as an event whatever the group randomized.

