According to recent large European cohorts, we estimate that the primary endpoint rate in our control group will be 1.5 % [35, 36, 39]. To be regarded as non-inferior, the maximal difference in proportions between 2 groups (Delta) should not exceed 1.5 % – an absolute primary event rate of 3 % in the intervention group. This failure rate corresponds to the upper bound of the observed rate after a negative CPTA and is a widely accepted criterion for the validation of diagnostic strategies for PE [40]. This rate is in line with previous landmark studies that comprise the basis of our current understanding.

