### Sample size under non-inferiority hypothesis

To assess non-inferiority of the “PERC strategy,” with 1-sided alpha = 5 %, beta = 20 %, *N1* = 1624 subjects are needed (East 6, Cytel, Cambridge, MA, USA). A cluster is a 6 months period for 1 site. Under the assumption of an intraclass correlation coefficient of 0.002, an intra-period correlation of 0.001 and a mean cluster size for one period of 60 patients, the cluster design effect would be of *D* = 1.118. Considering 5 % of non-evaluable subjects, with 15 sites involved in the trial, which corresponds to 30 clusters, 61 subjects per site per period are required and will lead to a total of 1920 patients.

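### The site-level GEE rests on 15 sites; run in its usual form, without a small-sample correction, its 5 % superiority tests would reject falsely about 8 % of the time

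*Protocol article*

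**What the plan says.** The Statistical analysis section of the protocol article bases the non-inferiority decision on a simple interval: "The decision rule will be based on the upper bound of the 90 % 2-sided CI of the difference of percentage of VTE events" between groups, judged against a margin of 1.5 percentage points. To allow for cluster randomization it then adds that "confirmatory analysis will be performed using a generalized estimating equation (GEE) assuming an exchangeable correlation matrix structure and considering clustering at the site level".

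The same method serves three secondary outcomes: "Unnecessary irradiative imaging, adverse events and deaths at 3 months will be compared using GEE assuming an exchangeable correlation matrix structure", again with clustering by site. The level is fixed: "All superiority tests will be performed at 5" %.

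The sample size section gives the number of units: "with 15 sites involved in the trial, which corresponds to 30 clusters, 61 subjects per site per period are required".

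The article does not say whether the GEE standard error is robust or model-based, or whether normal or t quantiles are used. It neither states nor excludes a small-sample correction.

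**The concern.** In its usual form a GEE takes its standard error from the spread of the site-level residual totals (the sandwich estimator) and refers the result to the normal distribution. Both steps are justified for a large number of clusters. Clustering here is by site, so the 30 site-periods supply only 15 independent units. With so few, the sandwich variance is biased low and normal quantiles are too short, and both errors make intervals too narrow.

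The test of unnecessary imaging is the most exposed. Reducing such imaging is among the first-listed secondary objectives, and the GEE is the only test named for it. The confirmatory analysis of the primary outcome is the plan's named allowance for clustering, so it should not be more lenient than the unadjusted interval beside it.

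**Working it through.** **The plan's own figure.** With 1.5 % in both groups, a margin of 1.5 points, one-sided alpha of 5 % and power of 80 %:

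n per arm = 2 × 0.015 × 0.985 × (1.645 + 0.842)² / 0.015² ≈ 812, so 1624 in total, as stated.

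The design effect is 1 + 59 × 0.002 = 1.118, as stated. The inputs are therefore read correctly.

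**Few-sites effect, analytically.** Let d_k be the intervention-minus-control difference within site k, with K = 15 equal sites and S² the usual sample variance of the d_k. The treatment estimate is the mean of the d_k. The uncorrected sandwich variance is Σ(d_k − mean)² / K² = S²(K − 1)/K². The z statistic is then the ordinary t statistic on K − 1 = 14 degrees of freedom, multiplied by √(K/(K − 1)) = √(15/14). For roughly normal d_k:

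- Two-sided 5 %: P(|t14| > 1.960 × √(14/15)) = P(|t14| > 1.894) = **7.9 %**
- One-sided 5 %: P(t14 > 1.645 × √(14/15)) = P(t14 > 1.589) = **6.7 %**

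No assumed correlation or event rate enters these two figures.

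**Superiority tests, simulated with no true effect.**

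| Setting | Uncorrected sandwich, normal quantiles | K/(K − 1) factor, t on 14 df |
|---|---|---|
| Planned correlations, equal sites | 7.2–7.8 % | 4.3–5.0 % |
| Assumed 15 % imaging rate | 7.9–8.7 % | 5.0–5.7 % |

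Uncorrected, unequal sites give 8–9 %, and larger assumed correlations (0.02 and 0.01) give 8–13 %.

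**Confirmatory check at the margin.** The setting is 15 sites × 2 periods × 61 patients, correlations 0.002 and 0.001, and true rates of 1.5 % (control) and 3.0 % (intervention). A pass is an upper 90 % limit below 1.5 points. False passes with fitted exchangeable GEEs (identity link, no period term, 6,000 trials):

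| Standard error and quantile | False pass |
|---|---|
| Uncorrected sandwich, normal | 8.2 % |
| Model-based, normal | 6.9 % |
| Mancl-DeRouen, normal | 6.8 % |
| Mancl-DeRouen, t on 14 df | 5.8 % |

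The Monte Carlo standard error of the first row is √(0.082 × 0.918 / 6000) ≈ 0.35 points. Across equal and unequal sites and correlations from 0 to 0.002, the uncorrected version ranged from 7.5 to 8.9 %. Its standard error averaged about 0.95 of the true one with equal sites and 0.91–0.93 with unequal sites.

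**Split of the excess.** Few sites account for the step from 5 % to 6.7 %. The step from 6.7 % to about 8 % comes from rare, skewed event counts, which is why about 6 % remains after correction.

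**Joint with the primary rule** (60,000 simulated trials, same setting): the unadjusted interval passes falsely in 6.3 %, the uncorrected site-clustered check in 7.8 %, and both together in 5.5 %. With a corrected check the joint figure is 4.7 %.

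**Width of corrected intervals.** √(15/14) × 1.761/1.645 = 1.11 for a 90 % interval; √(15/14) × 2.145/1.960 = 1.13 for a 95 % interval.

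**The case against.** The strongest objection is that this treats silence as error. A condensed article commonly leaves the variance estimator and reference distribution to the SAP, which is not shown, and a site-level GEE is fully compatible with a corrected variance and t limits. That stands to this extent: a reader might infer that the plan has chosen to do without a correction, and the text does not support that. The 8 % is conditional on the usual uncorrected analysis. The point survives because the article itself fixes the method, the clustering level, the number of sites and the 5 % levels. Following the named method in its usual form misses those levels, and even a model-based standard error with normal quantiles gave 6.9 % for the confirmatory check.

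A reader might also infer that the trial would declare false non-inferiority 8 % of the time. The documents do not support that either. The decision rests on the unadjusted interval, and a GEE used as a second hurdle lowers the joint rate to about 5.5 %, even uncorrected.

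Two further objections stand. The number of sites does not explain all of the excess in the confirmatory check. The imaging rate and the larger correlations are assumptions from outside the documents, although the analytic 7.9 % does not depend on them.

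**Conclusion.** The point holds conditionally. If every GEE uses an uncorrected sandwich standard error and normal quantiles, the two-sided superiority tests run at about 8 % instead of 5 %: 7.9 % with equal sites, about 8–9 % with unequal sites. The confirmatory check taken alone falsely passes at the margin about 8 % of the time. The primary decision is not itself affected, so the main gain from a correction is for the superiority tests.

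The analytic figures assume equal sites and roughly normal site differences. The simulations assume beta or gamma site effects, no period term and, where sites are unequal, a coefficient of variation in size of 0.5–0.8. They were not run on any observed data.

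**What to change.** Add one sentence to the Statistical analysis section: every GEE uses a bias-corrected sandwich variance (for example Mancl-DeRouen or Kauermann-Carroll) with t quantiles on number of sites minus 1 degrees of freedom. If the SAP already says so, the article needs only to be consistent with it.

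This brings the superiority tests to about 5 % (5.0–5.7 % simulated) and the standalone confirmatory check to about 6 %. The cost is intervals about 11 % (90 %) to 13 % (95 %) wider, and simulated power of the confirmatory check falling from about 83 % to 79 %, close to the planned 80 %. No change to design or sample size is needed.

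### Counting every missing outcome as a VTE in both arms costs the secondary ITT analysis power, and makes it follow any follow-up imbalance

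*Protocol article*

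**What the plan says.** All statements are in the protocol article. Under Statistical analysis, the primary analysis is per-protocol: "analysis of the principal criterion will be performed on a per-protocol population". The ITT analysis of the same endpoint is secondary. Replacement of missing data is confined to it: "Missing data will not be replaced except for the principal criteria for the secondary ITT analysis". The replacement rule then follows: "Missing value will be considered as an event whatever the group randomized". No reason is given for the rule.

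The same section sets the scale. On the control rate: "we estimate that the primary endpoint rate in our control group will be 1.5" %. On the margin: "the maximal difference in proportions between 2 groups (Delta) should not exceed 1.5" %. On the decision: "The decision rule will be based on the upper bound of the 90 % 2-sided CI of the difference of percentage of VTE events between groups".

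Under Sample size under non-inferiority hypothesis, the calculation is made "with 1-sided alpha = 5 %, beta = 20" %. It allows for 5% "non-evaluable subjects, with 15 sites involved in the trial, which corresponds to 30 clusters", and the stated total is 1920 patients.

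**The concern.** A rule that turns each missing outcome into a failure is often taken to be cautious. That needs checking here, because VTE is expected in only 1.5% of patients. Even modest loss to follow-up would then add more artificial events than there are real ones. Those events inflate the variance of the difference. If the arms lose patients at different rates, the artificial events also move the difference itself.

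In a non-inferiority trial the ITT result is read beside the per-protocol result, and agreement between them is part of the evidence. Per-protocol replaces nothing, so this ITT analysis is the only one in the article with a stated way of handling missing primary outcomes. If it disagreed with the per-protocol result, the cause could be the imputation rule alone. If it agreed, that could reflect heavier losses in the control periods.

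**Working it through.** **Reproducing the plan's figure.** With both rates at 1.5%, margin 1.5 points, one-sided alpha 5% and power 80%:

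n per arm = (1.645 + 0.842)² × 2 × 0.015 × 0.985 / 0.015² = 812, so 1624 in total, as stated.

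Design effect D = 1 + (60 − 1) × 0.002 = 1.118, as stated. Then 1624 × 1.118 / 0.95 = 1911, and 64 per site and period × 30 = 1920. (The stated 61 × 30 gives 1830. I use the stated total, which favours the plan.)

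**Inputs and assumptions.** About 960 per arm: 1920 / 2, with 1:1 implied because every site runs both periods. True VTE rate p = 1.5%. The missing share m is not given in the article, so a range is shown. The ITT analysis is assumed to use the same 90% interval and margin.

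**Equal missingness, identical arms.**

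- ITT event rate: p* = m + (1 − m)p
- Imputed share of events: m / p*
- Half-width: 1.645 × √(2p*(1 − p*)D / 960)
- Chance of showing non-inferiority: Φ(0.015 / SE − 1.645)

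Paired entries are for D = 1 and D = 1.118.

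| m | p* | Imputed share | Half-width (points) | Chance of non-inferiority |
|---|---|---|---|---|
| 0 | 1.5% | 0 | 0.91 / 0.97 | 85.5% / 81.9% |
| 1% | 2.485% | 40% | 1.17 / 1.24 | 67.9% / 63.7% |
| 2% | 3.47% | 58% | 1.37 / 1.45 | 56.0% / 52.1% |
| 3% | 4.455% | 67% | 1.55 / 1.64 | 47.9% / 44.5% |
| 5% | 6.425% | 78% | 1.84 / 1.95 | 38.0% / 35.3% |
| 10% | 11.35% | 88% | 2.38 / 2.52 | 27.1% / 25.3% |

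At m = 5% this is 960 × 0.05 = 48 imputed events per arm, against 912 × 0.015 ≈ 14 real ones. The half-width exceeds the margin, so an observed difference of zero would fail. Restoring 80% power would take about 6610 patients before the design effect, against 1624.

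Imputed events equal real ones when m = 0.015(1 − m), that is m = 0.015 / 1.015 ≈ 1.5%. The chance of success falls below one half above about 2.7% missing (D = 1) or 2.2% (D = 1.118).

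**Equal missingness, PERC truly 1.5 points worse (3.0% v 1.5%).** The difference becomes (1 − m) × 1.5. At m = 5% that is 0.95 × 1.5 = 1.43 points, and false non-inferiority rises from 5% to 5.7%. The dilution is slight.

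**Unequal missingness.** With equal true risk, the ITT difference is (m_PERC − m_control) × (1 − 0.015). One point more missing in control gives −0.01 × 0.985, about −0.99 points. The ranges below span the two values of D.

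- Equal true risk, 5.5% missing in PERC v 4.5% in control: 11–12% chance of showing non-inferiority.
- Equal true risk, 4.5% v 5.5%: 68–72%.
- True rates 3.0% v 1.5%, 4.5% v 5.5% missing: the difference is (0.045 + 0.955 × 0.03) − (0.055 + 0.945 × 0.015) = 0.45 points, with false non-inferiority at 21–23%.

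**Comparison with milder handling.** With 5% missing in both arms, identical true rates and D = 1.118, analysing the 912 observed per arm gives 80% power. Giving missing patients 1, 2, 5 or 10 times the 1.5% risk gives 82%, 80%, 76% or 69%. (These four treat imputed values as observed, so they are somewhat optimistic.) The stated rule gives 35%.

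**The case against.** The rule touches only a secondary analysis. A reader might infer that the trial's main non-inferiority decision is distorted. The article does not support that, because the per-protocol analysis decides and uses no imputed events. Nor can it be said that the confirmatory GEE inherits the rule, since its population is not stated.

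The 5% figure is an allowance for non-evaluable subjects in a trial with a per-protocol primary analysis. It may include protocol deviations, or patients whose PE was found at the first visit and who fall outside the endpoint. Follow-up uses the patient, the general practitioner and medical records (Trial objectives and outcomes), so true missingness may be well below 5%. It would therefore be wrong to say that the ITT analysis will usually miss the margin when the strategies are identical. That holds only above roughly 2.2–2.7% missing.

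It is also tempting to say that the ITT analysis tests follow-up completeness instead of safety. With balanced losses it does not: the harm is mainly lost power, which errs toward not declaring non-inferiority, and meeting the margin under such losses would be supportive. The article predicts no imbalance, and each site delivers both strategies with the same follow-up procedure.

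These points limit the severity and the wording, and they stand. They do not rescue the rule, which is stated outright and already makes 40% of events artificial at 1% missing. A worst case for the new strategy would count missing as an event in the PERC arm only. Applied to both arms, the rule can favour either strategy. The strategies run in separate six-month periods at each site, so unequal follow-up cannot be excluded.

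**Conclusion.** The concern holds for the secondary ITT analysis and should be fixed. It does not reach the per-protocol primary analysis. At a 1.5% event rate the rule costs substantial power when losses are equal. When losses differ, the estimate follows the imbalance almost point for point, in either direction.

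The power figures rest on about 960 per arm, a true rate of 1.5% in both arms, a normal approximation and D between 1 and 1.118. The 5% scenario also assumes that all non-evaluable subjects are missing outcomes. The conclusion does not depend on that last assumption, but the size of the loss does. The imbalance scenarios are illustrations, not forecasts.

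**What to change.** Do not use missing = event in both arms as the ITT estimate. Base the secondary ITT estimate on patients with observed outcomes, or on a parsimonious imputation by arm with very few predictors, for example PERC status and age. Leave site and period out as fixed effects. Within an arm each site contributes a single period, so the two are redundant, and about 14 events per arm cannot support a model with 15 sites plus several covariates.

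Add a tipping-point analysis that varies the assumed VTE risk of missing patients separately in each arm and includes missing = event in the PERC arm only. Keep missing = event in both arms as one labelled extreme scenario.

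The cost is a change of wording and a little more analysis; no new data are needed. The central ITT estimate would then rely on outcomes being missing at random, and the tipping-point analysis tests that reliance. The change should be made before outcomes are examined by arm. The article gives the trial as recruiting, with no interim analysis planned.

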### Sample size under non-inferiority hypothesis

To assess non-inferiority of the “PERC strategy,” with 1-sided alpha = 5 %, beta = 20 %, *N1* = 1624 subjects are needed (East 6, Cytel, Cambridge, MA, USA). A cluster is a 6 months period for 1 site. Under the assumption of an intraclass correlation coefficient of 0.002, an intra-period correlation of 0.001 and a mean cluster size for one period of 60 patients, the cluster design effect would be of *D* = 1.118. Considering 5 % of non-evaluable subjects, with 15 sites involved in the trial, which corresponds to 30 clusters, 61 subjects per site per period are required and will lead to a total of 1920 patients.

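### Sample size: 61 subjects per site per period gives 1830 patients, not the stated 1920; the total is right and corresponds to 64 enrolled (61 evaluable) per site per period

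*Protocol article*

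**What the plan says.** All the figures are in the protocol article, in the Statistical analysis section and the section on sample size under the non-inferiority hypothesis.

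- Event rate: "we estimate that the primary endpoint rate in our control group will be 1.5" per cent.
- Margin: "the maximal difference in proportions between 2 groups (Delta) should not exceed 1.5" per cent.
- Error rates and size before clustering: "with 1-sided alpha = 5 %, beta = 20 %, *N1* = 1624 subjects are needed".
- Correlations: "intraclass correlation coefficient of 0.002, an intra-period correlation of 0.001".
- Cluster size and design effect: "a mean cluster size for one period of 60 patients, the cluster design effect would be of *D* = 1.118".
- Allowance for losses: "Considering 5 % of non-evaluable subjects". This clause opens the sentence that gives the per-site number and the total.
- Number of clusters: 15 sites with two periods each, stated as 30.
- Result: "61 subjects per site per period are required and will lead to a total of 1920 patients".

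The decision rule agrees with the one-sided 5 % level used for the sample size: "The decision rule will be based on the upper bound of the 90 % 2-sided CI". The section does not label 61 as either enrolled or evaluable, and the figure 64 does not appear.

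**The concern.** The per-site number and the total stand in one sentence and are said to follow from each other, but with 30 site-periods they do not. The gap of 90 patients is too large for rounding. Because the sentence begins with the 5 % allowance, the natural reading is that 61 already contains it and is therefore the number to enrol.

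At stake is which number a site works to. A site that took 61 as its enrolment figure would leave out the allowance for non-evaluable patients. That allowance matters here because the primary analysis is per protocol and counts failures only among patients in whom PE was initially ruled out. Each strategy also has its own period at each site, so a shortfall in one period cannot readily be made up in the other.

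**Working it through.** **Inputs.** Event rate 1.5 % in both groups (the stated control rate, with no true difference assumed); margin 1.5 percentage points; one-sided alpha 5 %; power 80 %; ICC 0.002; mean cluster size 60; 5 % non-evaluable; 30 site-periods. Equal allocation is assumed, since each site has one period of each strategy.

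**Step 1: size before clustering.**
n per arm = (1.645 + 0.842)² × 2 × 0.015 × 0.985 / 0.015² = 812, so N = 1624. This matches the article.

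**Step 2: design effect.**
D = 1 + (60 − 1) × 0.002 = 1.118. This matches the article.

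**Step 3: evaluable subjects needed.**
1624 × 1.118 = 1815.6. Per site-period: 1815.6 / 30 = 60.5, rounded up to **61**.

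**Step 4: enrolled subjects needed.**
1815.6 / 0.95 = 1911.2. Per site-period: 1911.2 / 30 = 63.7, rounded up to **64**. Total: 64 × 30 = **1920**. This matches the article.

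**Step 5: the sentence as written.**
61 × 30 = **1830**. The shortfall is 1920 − 1830 = 90, and 90 / 1920 = 4.7 %.

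So 61 comes from Step 3, before the allowance, and 1920 comes from Step 4, after it.

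**Step 6: power under each reading.** Normal approximation with unpooled variance:
power = Φ(0.015 / SE − 1.645), where SE = √(2 × 0.015 × 0.985 / n) and n is half the effective total (evaluable subjects divided by 1.118).

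| Reading | Enrolled | Evaluable | Effective total | Power |
|---|---|---|---|---|
| 64 enrolled per site-period | 1920 | 1824 | 1631 | 80.2 % |
| 61 evaluable per site-period | not fixed by this reading | 1830 | 1637 | 80.3 % |
| 61 enrolled per site-period | 1830 | 1738.5 | 1555 | 78.5 % |

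Only the last row falls below the planned 80 %. There, 1738.5 evaluable subjects stand against the 1815.6 needed.

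**The case against.** The strongest reply is that the planned size is sound. The total of 1920 follows exactly from the stated inputs, and 61 is called required, not an enrolment target or a cap. Read as evaluable subjects, it costs no power. All of this stands, and it limits the point to one mislabelled figure. It does not remove the contradiction, because the sentence introduces 61 with the 5 % allowance and then says that 61 leads to 1920.

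A reader might infer more than the article supports, in three ways.

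- *The trial is underpowered.* This does not follow. The loss arises only if 61 is used as the enrolled number at D = 1.118, and even then it is about 1.5 points.
- *Period length and site closure depend on 61.* The article fixes each period at six months by calendar and defines a cluster as such a period at one site. Nothing ties the length of a period or the closing of a site to a patient count, and no site target appears elsewhere.
- *61 is the right enrolled number under a smaller design effect.* The section lists a second correlation, 0.001, which the stated D does not use. To credit it would require an assumption about what it measures that the article does not give. It would also not rescue the sentence, since 61 enrolled in each of 30 site-periods is still 1830.

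**Conclusion.** The sentence is wrong as written: 61 per site per period gives 1830 patients, not 1920. On the stated inputs the total is correct and belongs with 64 enrolled per site-period, while 61 is the evaluable number before the 5 % allowance.

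The consequence is small and conditional. Used for enrolment, 61 would leave the trial 90 patients (4.7 %) short, with power of about 78.5 %. Used as the evaluable number, it keeps power at about 80.3 %. These power figures rest on the stated event rate, margin and design effect, equal allocation, exactly 5 % non-evaluable and a normal approximation. The article does not show that any site recruits to 61, so the shortfall is a risk created by the wording and not an established defect of the design.

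**What to change.** Replace the per-site figure so that the sentence states 64 patients enrolled (61 evaluable) per site per period, total 1920. If sites have been given recruitment targets, check that they are set at 64. The cost is the correction of one sentence and, if needed, of the site targets. The total, margin, alpha and analysis do not change.
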